## Abstract

**Background:**

Depending on the definitions used, between 5 and 20 % of all Swedish children grow up with at least one parent suffering from alcohol problems, while 6 % have at least one parent who has received inpatient psychiatric care, conditions that may affect the children negatively. Nine out of ten Swedish municipalities therefore provide support resources, but less than 2 % of these children are reached by such support. Delivering intervention programs via the Internet is a promising strategy. However, web-based programs targeting this at-risk group of children are scarce. We have previously developed a 1.5-h-long web-based self-help program, *Alcohol & Coping*, which appears to be effective with regards to adolescents’ own alcohol consumption. However, there is a need for a more intense program, and therefore we adapted *Kopstoring*, a comprehensive Dutch web-based psycho-educative prevention program, to fit the Swedish context. The purpose of the program, which in Swedish has been called *Grubbel*, is to strengthen protective factors, such as coping skills and psychological well-being, prevent the development of psychological disorders, and reduce alcohol consumption.

**Methods/design:**

The aim of the current study is to evaluate the effectiveness of *Grubbel*, which targets 15–25-year-olds whose parents have substance use problems and/or mental illness. Specific research questions relate to the participants’ own coping strategies, mental health status and substance use. The study was initiated in the spring of 2016 and uses a two-armed RCT design. Participants will be recruited via social media and also through existing agencies that provide support to this target group. The assessment will consist of a baseline measurement (t0) and three follow-ups after six (t1), 12 (t2), and 24 months (t3). Measures include YSR, CES-DC, Ladder of Life, Brief COPE, AUDIT-C, and WHOQOL-BREF.

**Discussion:**

Studies have revealed that the majority of children whose parents have substance use or mental health problems are not reached by the existing support. Thus, there is an urgent need to develop, implement, and evaluate novel intervention programs and disseminate successful programs to a broader audience. This study, investigating the effects of a web-based intervention, therefore makes an important contribution to this field of research.

**Trial registration:**

ISRCTN10099247. Retrospectively registered on August 31, 2016.

## Background

Children growing up in families with parental substance use problems or mental illness are at risk for a number of psychological problems (reviewed in e.g., [1–3]), including depression and anxiety disorders, as well as behavioural problems [3–5]. Furthermore, these children may also experience poor intellectual, cognitive, and academic achievement [6, 7], domestic physical abuse [8], and are at risk for earlier drinking onset [9] and for developing substance use problems themselves [10–12]. Children affected by parental substance use problems or mental illness therefore comprise a target group for selective intervention and prevention strategies (reviewed in e.g., [13, 14]).

International estimates have revealed that the problem is widespread, and the proportion of children with at least one parent with substance use problems ranges from about 8 to 30 % [13, 15–18], while about 12–39 % have at least one parent with a mental health problem [19–22]. Reasons for the variation in the figures may include how the problem is defined, the methodology of data collection, and cultural differences. In line with this, Swedish estimates have revealed that approximately 5 % of all children have at least one parent with a substance use disorder [23], while 17–20 % grow up in families where at least one parent has risky alcohol consumption or substance use problems [24–26]. Moreover, about 6 % of all Swedish children have at least one parent who has received inpatient psychiatric care [25].

The Swedish municipalities alone account for the vast majority of support offered to children whose parents have substance use problems or mental illness. In fact, during 2015, more than 90 % of all municipalities provided support resources or referred children of substance-abusing parents to adequate support [27]. The corresponding number concerning support for children whose parents have mental illness was 73 % in 2009 [28]. However, the vast majority of children affected by parental problems are not reached by the existing support, and estimates reveal that not even 2 % of all children growing up with parental substance use problems receive support. Thus, there is a tremendous gap between those who might be in need of support and those who actually receive it, and reasons to this gap may be attributed to problems with accessibility of intervention programs and difficulties in identifying and attracting children into these programs [13, 24].

Digital interventions delivered via for instance the Internet or mobile phone applications provide one promising way to reach out and support a larger number of individuals (reviewed in [29–31]). With regards to adolescents and young adults, this seems attractive since they generally have great experience with digital technology and social media. Furthermore, research has shown that adolescents regard the Internet as particularly appealing since it provides an accessible and anonymous way of seeking help [32]. Web-based interventions targeting a wide range of conditions have also been found to be effective, which was concluded in a comprehensive review covering 92 studies including a total of 9764 participants, where the mean effect size was found to be similar to that of traditional “face-to-face” therapy [33]. It should be noted that the vast majority of digital interventions reported in the literature have been designed for and tested on adults. However, although the number of web-based interventions targeting children or adolescents is increasing [34–40], the number of interventions aimed at children whose parents have substance use problems or mental illness is still scarce [13, 41–43].

We have previously developed a web-based therapist-guided self-help program called *Alcohol & Coping*, which targets 15–19-year-olds with at least one parent with alcohol problems. The intervention has been evaluated in a randomized controlled trial (RCT), which revealed that about 40 % of the adolescents in the study had self-reported risky alcohol consumption at the baseline assessment (personal communications [name]). Results further revealed that the intervention appeared to be effective with regards to adolescents’ own alcohol consumption. However, *Alcohol & Coping* is a relatively brief intervention (about 1.5 h) and there is a need for a more intense program. We have therefore translated and culturally adapted a comprehensive Dutch web-based group prevention program called *Kopstoring* into a Swedish context. *Kopstoring* is based on psycho-educative principles, and consists of eight weekly online chat group meetings, each lasting for about 1.5 h, and an additional ninth follow-up meeting. Each meeting focuses on a particular theme and is moderated by one or two trained professionals. The *Kopstoring* program is currently being evaluated in the Netherlands [42, 44]. The present text reports on the design of a study investigating the effectiveness of the Swedish version of *Kopstoring*, called *Grubbel*.

### Objective and research questions

The main objective of this study is to evaluate the effectiveness of the group intervention *Grubbel* targeting 15–25-year-olds with at least one parent with a substance use problem or mental illness. We hypothesize that in comparison with a control group who receives care as usual (CAU), participants in the intervention group will show improved coping skills, reduced symptoms of depression and behavioural problems, improved quality of life, and a reduction in alcohol consumption.

Another objective is to study the intervention implementation as regards the intervention’s content and structure and its feasibility in use. What has been successful in the interaction between participants and the moderators, which were the facilitating and hindering factors of implementation, and what can be said about the applicability of the technical intervention platform?

## Methods/design

The study was initiated in April 2016 and consists of a quantitative two-armed RCT (Fig. 1) and a qualitative implementation study.

**Fig. 1 Fig1:**
[figure not shown]
Flow-chart diagram depicting the design of the study. The participants are unequally allocated (ratio 1.8) in favour of the intervention group

### The target sample

The aim is to include at least 140 adolescents (aged 15–25 years) who perceive at least one parent to have a substance use problem and/or mental illness. Additional inclusion criteria (Fig. 1) are as follows: having access to a device, such as a computer or tablet with internet access, being fluent in Swedish, and having consented to participate. Participants who reveal symptoms of severe depression or show indications of either suicidal or self-injurious behaviour will be excluded from the study and referred to appropriate care.

### Recruitment and screening

Participants will be recruited primarily via social media (i.e., Facebook and Instagram) and also through existing agencies, authorities, and organisations such as health care centres, social services, non-profit organizations, and self-help groups aimed at adult children of alcoholics, which all have in common that they provide support to this target group.

Those who are interested in participating will be referred to the study webpage (www.grubbel.nu), which contains further information about the study and a link to an online screening survey. In addition to demographic questions such as age and gender, the participants will be screened for having parents with alcohol problems through the Children of Alcoholics Screening Test (CAST-6). The CAST-6 is a six-item measure originally designed to assess whether or not individuals perceive their parents’ alcohol consumption as problematic, and has been proven to be a useful screening instrument which compares well with other measures [45, 46]. The CAST-6 is reliable (*r* = 0.94), has high internal consistency (*r* > 0.92), and is valid (*r* = 0.93) as compared with the original 30-item version using the recommended cut-off score of 3 or higher [45, 46]. The participants will also be asked to respond to the question: “Do you perceive any of your parents to have a mental illness?”.

Those who have 3 or more points on the CAST-6 or answer yes to the question on parental mental illness will be asked to answer questions concerning their motivation and possibility to participate in the group course on a weekly basis, and also to fill out the CES-DC questionnaire, which measures symptoms of depression (see below). Those who have at least one parent with a substance use problem or mental illness, who are motivated and have the opportunity to participate in the group course on a weekly basis, and do not have symptoms of severe depression as measured by the CES-DC, will be asked to consent to study participation and provide an e-mail address.

### Assessment

The assessments for this study will consist of a baseline measurement (t0), which will take place before randomization, and three follow-up measurements after six (t1), 12 (t2), and 24 months (t3). Participants will be invited to each assessment by e-mail, and if necessary up to three reminders will be sent at five, ten, and 15 days after the first invitation, respectively. All assessments will be in the form of an online survey distributed via the survey data collection tool Easyresearch (QuestBack, Norway). In order to increase the response rate, participants will be offered an incentive of one cinema gift certificate, corresponding to approximately 11 Euros, for each assessment. The resulting survey contains 216 questions and takes approximately 30 min to complete.

### Outcome measurements

#### Primary outcomes

To measure depressive symptoms during the preceding week, the Center for Epidemiological Studies Depression Scale for Children (CES-DC) will be used [47]. This scale consists of 20 items with response options on a four-point Likert scale. It measures depressive symptoms during the preceding week and is a valid measure of general childhood psychopathology [48]. The scale has shown high internal consistency (α = 0.91) and has been proven to be valid among Swedish adolescents when compared with the Beck’s Depression Inventory (*r* = 0.81) [49].

Participants’ coping strategies will be measured using the Brief COPE, which consists of 28 items using four-point Likert scales and has been proven to have acceptable high internal consistency (α = 0.58–0.92) [50, 51].

To measure quality of life, the World Health Organization’s Quality of Life Questionnaire (WHOQOL-BREF) will be used. The scale contains 26 items using five-point Likert scales and measures quality of life in four principal domains: physical health, mental health, social relations, and environment [52]. This instrument has demonstrated good to excellent psychometric properties with Cronbachs’s α ranging from 0.68 to 0.82, and construct validity (item-total correlations) with r ranging from 0.45 to 0.70 [53].

Alcohol consumption will be assessed using the short version of the Alcohol Use Disorders Identification Test (AUDIT-C) [54], assessing frequency of drinking, quantity consumed, and frequency of heavy episodic drinking (i.e., binge drinking). The instrument has shown satisfactory internal consistency (α = 0.80) and good validity (AUROC = 0.85) [55].

#### Secondary outcomes

Overall life satisfaction will be measured using the Ladder of Life, asking about each participant’s past, present, and future rating of his/her life. The original version was intended for adults and asks the respondents to reflect on their life over a 5-year perspective [56]. A modified version for children and adolescents, using a shorter timeframe of 1 year, will be used in this study [57].

To measure the participants’ competencies and behavioural problems, the Youth Self-Report (YSR) questionnaire will be used. It consists of 119 problem behaviour items that form internalizing and externalizing scales, and has been demonstrated to be valid and to have good internal consistency [58, 59].

#### Qualitative interviews

Focus group interviews will be conducted with the trained professionals who moderate the intervention program during the study. The interviews will be based on interview guides containing questions regarding for instance the intervention content and structure, and its feasibility in use. What has been successful in the interaction between the participants and the moderators? How well does the technical intervention platform work? What were the facilitating and hindering factors of implementing the intervention?

### Allocation/Randomization

Participants will be randomly allocated to one of the two study groups after completing the baseline assessment. An unrestricted random allocation sequence will be generated by an external researcher using the Random Allocation Software [60]. Participants will be informed about their allocation by e-mail. Those participants who are randomized to the intervention group will receive further information about the study and about being assigned to a *Grubbel* group. The participants can choose between different dates for the group course, so they start on a day of their preference. Information about how to access the group course will be sent to the participants by e-mail. All participants will receive information about other support and information available according to care as usual (CAU), as described below.

### The intervention

The program *Grubbel* is a manual-based and well-structured prevention program and consists of eight consecutive weekly online chat-meetings, each lasting 1.5 h, and a ninth follow-up meeting one week after the last meeting. The aim of *Grubbel* is to strengthen protective factors such as coping strategies and psychological well-being, to decrease alcohol consumption, and to prevent the development of psychological disorders. The meetings take place in an online group chat tool (Campfire, Basecamp, IL, USA). The group chat is password-protected and encrypted using SSL (Secure Sockets Layer) technology and the same 4–8 participants in each group meet one another online during each session. Each meeting is moderated by one or two trained professionals (prevention and social workers, and psychologists from mental health and addiction centres), who have previous experience from working with the target group, and have participated in a two-day *Grubbel* course held by our research group.

Each session focuses on a particular theme (Fig. 2) and the themes are: (1) getting acquainted with the home situation, (2) roles in the family, (3) thoughts and feelings, (4) questions and answers about mental health problems, (5) different behaviour patterns, (6) social networks, (7) leading your own life with regards to social networks, and (8) the future. The ninth session is a follow-up session. After each session, the participants are required to complete a homework assignment to be discussed at the subsequent session. Previous research conducted by our research group has revealed that adolescents whose parents suffer from alcohol problems have a high level of risky alcohol consumption (personal communications [name]). An addition to the original *Kopstoring* manual was therefore made, with the objective of providing structured information about risky use of substances, addiction, and heredity. The fourth theme was also modified to include questions and answers about risky alcohol use, addiction, and heredity (Fig. 2).

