### Sample size

The sample size calculation is based on the ability to detect a medium or larger effect size, corresponding to a standardized mean difference (Cohen’s d) of > 0.05 [61]. Based on differences between means, an *a priori* calculation of the estimated sample size, using the G*Power software [62], and accounting for an unequal allocation ratio of 1.8 in favour of the intervention group, reveals that 140 participants need to be included in the trial, 90 in the intervention group and 50 in the control group (power = 0.80, α = 0.05, 2-tailed).

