### Analyses

#### The effectiveness study

Data will be analysed according to the intention-to-treat (ITT) principle, accounting for all included participants regardless of whether or not they have responded to the follow-up assessments. Missing data will be handled using the Missing Value Analysis routine in the SPSS software (IBM SPSS Statistics 23, IBM Corporation, NY, USA).

Data analyses will consist of comparing outcome measurements at baseline (t0) and subsequent follow-up (t1, t2, and t3) assessments, with regards to within-group and between-group comparisons.

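### The stated 80% power treats all 140 participants as independent, although the intervention arm is treated in fixed chat groups of 4–8

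*Protocol article*

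**What the plan says.** Participants are randomized individually. Those allocated to Grubbel are then placed in groups, partly by their own choice of date: "The participants can choose between different dates for the group course" (Allocation/Randomization). Over eight weekly meetings and one follow-up meeting, "the same 4–8 participants in each group meet one another online during each session" (The intervention). One or two moderators lead each meeting, and homework is discussed in the group. The comparison arm has care as usual, and the trial forms no groups there (The control).

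The Sample size section takes a "medium or larger effect size, corresponding to a standardized mean difference (Cohen’s d) of > 0.05". The calculation is "Based on differences between means", uses G*Power, and is made "accounting for an unequal allocation ratio of 1.8 in favour of the intervention group". It concludes that "140 participants need to be included in the trial, 90 in the intervention group and 50 in the control group". The design values behind this figure are given as "power = 0.80, α = 0.05, 2-tailed". It mentions no ICC, design effect or number of chat groups.

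The analysis text (The effectiveness study) says that outcomes at baseline and follow-up are compared "with regards to within-group and between-group comparisons". Here group means study arm, not chat group. No test or model is named.

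**The concern.** People who spend nine meetings with the same peers and moderators, in groups formed partly by preferred date, can be expected to have somewhat correlated outcomes. The mean of 90 such people varies more than the mean of 90 independent people, while no such inflation is built into the control arm. A calculation that takes all 140 as independent then states more power than the design has.

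The same correlation matters for the analysis. A between-arm comparison that left out chat group would understate the standard error, and the error would run towards declaring Grubbel effective. The Implications for practice section makes national dissemination depend on that result.

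**Working it through.** **Inputs from the article.** Two-sided α 0.05; power 0.80; allocation 1.8:1; 90 + 50; chat groups of m = 4 to 8, so 90/8 ≈ 11 to 90/4 ≈ 23 groups. The standardized scale sets SD = 1.

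**Inputs assumed.**
- d = 0.5. The printed value is 0.05, but the text calls the effect medium, and only 0.5 reproduces 140. At d = 0.05 the control arm alone would need 4884, and 140 participants would give about 6% power.
- ICC 0.01, 0.05 and 0.10, since none is given.
- Equal total variance in both arms.

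**Step 1: reproduce the stated figure.** For independent observations, SE = √(1/50 + 1/90) = √0.03111 = 0.1764. The noncentrality is 0.5/0.1764 = 2.835 on 138 df, and power is 0.804. One step down, 49 + 89 gives 0.797. So 90 + 50 is the independent t-test answer, with 0.4 percentage points to spare. A 1:1 trial would need 64 + 64 = 128, so the extra 12 participants only pay for the unequal allocation.

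**Step 2: add clustering in the intervention arm only.**
- Design effect: DE = 1 + (m − 1) × ICC
- Variance of the difference: 1/50 + DE/90
- Satterthwaite df, with k = 90/m groups: (DE/90 + 1/50)² / [(DE/90)²/(k − 1) + (1/50)²/49]
- Type I error of a test that ignores chat group: 2 × [1 − Φ(1.96 × SE independent / SE clustered)]

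*Example, m = 6 and ICC 0.05.* DE = 1 + 5 × 0.05 = 1.25. Variance = 0.02 + 0.01389 = 0.03389, so SE = 0.1841, which is 1.044 times 0.1764. Noncentrality = 0.5/0.1841 = 2.716 on about 52 df, and power = 0.760. Type I error if chat group is ignored = 2 × [1 − Φ(1.96/1.044)] = 0.060.

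| m | ICC | DE | SE ratio | Power (t) | Type I error if chat group ignored |
|---|---|---|---|---|---|
| 4 | 0.01 | 1.03 | 1.005 | 0.794 | 0.051 |
| 4 | 0.05 | 1.15 | 1.026 | 0.777 | 0.056 |
| 4 | 0.10 | 1.30 | 1.052 | 0.756 | 0.063 |
| 6 | 0.01 | 1.05 | 1.009 | 0.789 | 0.052 |
| 6 | 0.05 | 1.25 | 1.044 | 0.760 | 0.060 |
| 6 | 0.10 | 1.50 | 1.086 | 0.725 | 0.071 |
| 8 | 0.01 | 1.07 | 1.012 | 0.783 | 0.053 |
| 8 | 0.05 | 1.35 | 1.061 | 0.742 | 0.065 |
| 8 | 0.10 | 1.70 | 1.118 | 0.694 | 0.080 |

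At ICC 0.01 a normal approximation still gives 0.805 to 0.800. The small loss in the t column there comes largely from having few groups, and so fewer degrees of freedom.

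**The case against.** The strongest objection concerns the analysis. A reader might infer that the trial's standard errors are too small and that its p values for every outcome are too optimistic. The article does not support that. It names no test, model or covariance structure, and a mixed model with a chat-group effect would fit its wording. Such detail is commonly left to an analysis plan, which is not shown here. The type I error figures are therefore conditional on an analysis that ignores chat group. The power statement does not depend on this: it is a completed calculation in the article, and it reproduces without any clustering.

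The second objection is that the ICC may be small. The programme lasts about nine weeks and the first follow-up is at six months, so no follow-up falls while the groups are meeting. This stands, and it is why the range starts at 0.01, where the loss is about 1 to 2 percentage points.

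Third, the control arm may not be wholly ungrouped, because group support is one form that usual care can take. Partial nesting describes what the trial itself creates and is a reasonable working model, not a certainty.

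Finally, the 1.8 ratio might be thought to cover the clustering. The article gives no such reason, and Step 1 shows that the extra participants are used up by the imbalance.

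**Conclusion.** The point holds for the stated power. The 90 + 50 is the independent-observations result, with almost nothing to spare, in a trial whose intervention arm is treated in fixed groups. With d = 0.5 and equal total variances, power across groups of 4 to 8 is about 0.79–0.78 at ICC 0.01, 0.78–0.74 at 0.05 and 0.76–0.69 at 0.10. The ICC is assumed throughout, so the loss may be minor or may reach about 11 percentage points within this range. Inflating all 140 participants would overstate it, because the design effect applies to one arm. Loss to follow-up is a separate matter and plays no part in these figures.

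For the analysis the conclusion is only conditional: if chat group is ignored, type I error would lie between about 0.051 and 0.080 over the same range. This should be corrected, but it does not invalidate the trial.

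**What to change.** 1. Keep each participant's chat-group identifier in the trial dataset. It may be hard to recover later.
2. State that between-arm effects will be estimated with a partially nested mixed model: a random chat-group effect in the intervention arm only, controls as singletons, and a small-sample degrees-of-freedom correction. Satterthwaite and Kenward-Roger are both acceptable. If the analysis plan already says this, a cross-reference is enough.
3. Restate the power of 90 + 50 with the intervention-arm design effect, over ICC 0.01 to 0.10 and group sizes 4 to 8. Correct the printed effect size of 0.05 in the same place, or explain it.

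The cost is one stored variable, a few sentences, slightly wider confidence intervals and a slightly lower stated power. Nothing changes for participants, and no further recruitment is implied.
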